**6. Monitoring and audit**

Monitoring and audit are not planned.

**7. Report to the research manager of the institute**

According to the procedure document, we will report our study progress to the institute's research manager using the research ethics online system.

**8. Fund and conflict of interest**

This research will be conducted under Yokohama city's "Model project of Social Impact Bond." The graduate school of medicine, the University of Tokyo, will conduct this research as contract research from Yokohama city. The University of Tokyo is funded by Yokohama city to conduct this research.

In addition, the University of Tokyo is provided free online medical consultation services, “Syounika Online/Sanfujinka Online” and “Josanshi chat Soudan,” to conduct this research from Kids Public Inc., which is contracted with Yokohama city.

As for conflict of interests, principal researcher [name], co-researcher [name], and co-researcher [name] do not get any reward or have no equities from Kids Public Inc. or Yokohama city.

**Summary of changes to the protocol**

Version 1.0 and 2.0 were approved before starting the recruitment.

**•Version 1.0**

The first version of the study protocol was approved by the ethical review board of the University of Tokyo on March 16, 2020.

**•Version 2.0 (approved on August 30, 2020)**

The following changes were made to the protocol.

1. The condition "women in early pregnancy (first trimester)" was added to the inclusion criteria.
2. The recruitment period was changed from between July 1, 2020, and November 30, 2020, to between September 1, 2020, and January 31, 2021, because of the operation change of the founder and the service provider.
3. The timing to answer the baseline questionnaire, except for age, parity, household size, and expected birthday was changed from before to after randomization because of operational difficulties.

We registered our trial to the UMIN-CTR Clinical Trial (identifier: UMIN000041611) on August 31, 2021.

Version 3.0 and 4.0 were approved after starting the recruitment.

**•Version 3.0 (approved on October 21, 2020)**

The following changes were made to the protocol.

1. The inclusion criteria were changed from "women in early pregnancy" to "all pregnant women whose expected date of delivery was until October 31, 2021," due to the small sample size.
2. The recruitment period was expanded until August 31, 2021.
3. We added several recruitment methods such as announcements on the website and official SNS of Yokohama city, recruitment articles in ward newsletters, recruitment in the mother preparation class or childcare support site, and placement of leaflets at obstetric clinics or hospitals.
4. The details of secondary outcomes were added.

**•Version 4.0 (approved on January 15, 2021)**

The following changes were made to the protocol.

The recruitment field was expanded from Kohoku ward to all wards in Yokohama city.

The wording of descriptions was changed to reflect the abovementioned protocol changes.

**Statistical analysis plan**

The details of the descriptions of the statistical analysis plan in the study protocol are as below.

•Estimating confidence intervals

We planned to conduct modified Poisson regression models to estimate confidence intervals for binary outcomes and linear regression models for continuous outcomes.

•Conducting subgroup analyses

We planned to perform subgroup analyses using the same primary analysis model with the interaction term of intervention and pre-specified subgroups. Our pre-specified subgroups include age (< 18 years or older), parity (primipara or multipara), income (tertile among participants), education (< 18 years or longer), having elevated depressive symptoms at participation (Edinburgh Postnatal Depression Scale: EPDS < 13 or ≥ 13), past mental health problems and partnership (with or without a partner).

After enrolment, no woman younger than 18 was in our population, and only one participant did not have a partner. Therefore, we conducted a subgroup analysis using different age cut-off points: < 35 years or older, which was the definition of delayed childbearing by the Japan Society of Obstetrics and Gynecology. In addition, we did not conduct a subgroup analysis of partnerships because of the small sample size.

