**2-2. Methods**

(1) Research design

Prospective randomized-controlled trial

(2) Sample size

ⅰ) Numbers of study participants

Intervention group: 360

Control group：360

ⅱ)Rationale of sample size calculation

We calculated the required sample size as 249 in each group to detect differences in the proportion of women who were above a cut-off of the Edinburgh Postnatal Depression Scale: EPDS between 11% and 4% referring to the previous studies and preliminary program, with 5% two-sided significance level and 80% power. Considering the expected attrition rate as about 30%, We set the target sample size as 360 in each group.

ⅲ) Criteria

1. Inclusion criteria

Pregnant women living in Yokohama City whose expected date of delivery was before October 31, 2021.

1. Exclusion criteria

Women who don’t agree the participation.

Women who were not capable of communication in Japanese.

1. Analytic criteria (Participants who met this criteria will be excluded in the supplement analyses)

Miscarriage or stillbirth.

Baby enter the intensive care unit.

Participant get sick and hospitalize after childbirth.

Ongoing treatment of depression, bipolar disorder, or other psychiatric disease at the participation.

(3) Intervention

(1) Invasion to the participants: No

(2) Intervention to the participants: Yes

●Details of the interventions：Online medical consultation services “Syounika Online

/Sanfujinka Online”

In this study, we will provide online medical consultation services “Syounika Online/Sanfujinka Online” which the enterprise Kids Public Inc offers as an intervention. This service is delivered through the LINE platform. Women can consult with obstetrician-gynecologists, pediatricians, and midwives using this mobile service platform in the time women book by chat, call, or video call.

In addition, study participants can use “Josanshi chat Soudan,” in which women can consult with midwives about childcare or feeding by chat without booking after delivery. Furthermore, the enterprise will send the message that women can consult when they want and provide helpful information for women in childcare through the app.

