Pregnant women will spontaneously access the study website and be checked the eligibility on the website. After that, they read and understand the study protocol details, the offered intervention, randomization, and the deal of their personal information. We will inform the women that the study team of the University of Tokyo, Yokohama city, and Kids Public Inc. will share their minimum required private information to conduct this study. Women who want to participate in this study will agree with the participation and enter their personal information, including name, birthday, mail address, mobile phone number, postal code, expected day of delivery, parity, and family structure, on the website. After sending the agreement, an online system will immediately generate the study ID and 1:1 random allocation to either the intervention group or the control group without using any personal information. Participants will know their random assignment shown on the website and by e-mail.

After allocation, participants will receive an online questionnaire sent by e-mail from the study team of the University and answer it. This questionnaire will ask about baseline participants' information, such as the primary outcome of EPDS, gestational age, loneliness, past mental health problems, income, education, and social support.

Figure 3. Assumed image of the study website.

[figure not shown]

③ Details of information about the intervention group and the control group

1. The intervention group

Pregnant women in the intervention group will be provided the online consultation services, “Syounika Online/Sanfujinka Online” from the participation to four months after delivery, and the services “Josanshi chat Soudan” four months after delivery. Usually, these services need a usage fee; however, study participants can use them free without limitations on the number of times.

<Features of the intervention>

- Users can book any available time and consult anything they want for ten minutes during the service hours, which are Monday through Friday between 6 PM and 10 PM.
- Users can choose preferred methods, including voice calling, chat messaging, and video calling
- Users can also consult with midwives by chat without booking after the childbirth between 12 PM and 6 PM on the 2-3 times open weekday.
- Service provider constantly informs the users at least once a week that users can consult anything if they want through the platform.

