Figure 4. The image of online consultation services (Intervention group)

[figure not shown]
　　　
[figure not shown]

Women in the intervention group will get the online survey of EPDS two months after delivery offered by the service provider as a standard service. Women having high scores will be recommended to consult with professionals in the app.

1. The control group

Women in the control group cannot use the online consultation services above. Instead, they can use the website made by the research team of the University, which offers URLs of the useful public websites about pregnancy and childcare. Women in the control group also can get the online voucher after answering the baseline questionnaire.

Figure 5. The Image of the website offering the URLs of the useful websites (Control group)

[figure not shown]

Because this is an effectiveness study to evaluate the services, which have already been introduced in several public agencies or companies, women assigned to the control group can buy the services of their own will, and we will not prohibit it.

④ Online questionnaire of the outcomes three months after delivery

The research team of the University will get the childbirth date of all participants who submit the registration of birth to the public office from the agencies of Yokohama city with the participants’ agreement.

A research member will send an online questionnaire three months after delivery by e-mail. This questionnaire includes the primary outcome of EPDS and other outcomes such as self-efficacy, loneliness, and usage of the medical facilities. Participants will get an online voucher after answering this questionnaire regardless of the assigned groups.

⑤ Analytic methods

This study aims to assess the difference in the proportion of EPDS above the cut-off three months after delivery between the intervention group and the control group. Analyses will be conducted according to the intention-to-treat principle. We will conduct Fisher's exact test for the primary outcome. We will use a t-test or Mann-Whitney U test for the secondary outcomes according to the variable characteristics. The outcomes are bellow.

●Primary outcome

Proportion of the participants with the Edinburgh Postnatal Depression Scale (EPDS) above the cut-off three months after delivery（Cut-off points: nine or above）.

●Secondary outcomes

• Barriers to healthcare access

• Parenting self-efficacy

• Loneliness (the 3-items version of UCLA loneliness scale)

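### The plan names no covariates for the primary comparison, although age, parity and expected delivery date are recorded before allocation; adjusting for them is a modest efficiency gain

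*Combined protocol and SAP*

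**What the plan says.** Three parts of the combined document bear on this.

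- **Primary test.** Section 2-2 (4) ⑤ states "We will conduct Fisher's exact test for the primary outcome". The endpoint is binary, the EPDS at three months after delivery ("Cut-off points: nine or above").
- **Model for the interval.** The Statistical analysis plan adds "We planned to conduct modified Poisson regression models to estimate confidence intervals for binary outcomes", with linear regression for continuous ones. Subgroups are analysed "using the same primary analysis model with the interaction term of intervention and pre-specified subgroups". Neither sentence lists covariates or says whether the models are adjusted.
- **Allocation and baseline data.** Section 2-2 (4) ② describes "1:1 random allocation to either the intervention group or the control group without using any personal information", so nothing is balanced by design. Birthday, parity, expected delivery date and family structure are entered on the website before allocation. Women then learn their group on the website and by e-mail. The baseline questionnaire is e-mailed after allocation and covers items "such as the primary outcome of EPDS, gestational age, loneliness, past mental health problems, income, education, and social support". The Version 2.0 entry in the summary of changes agrees with this order.

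Section 2-2 (4) ③ and section 3 (2) describe a voucher for completing the baseline questionnaire for the control group only.

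**The concern.** Neither the design nor the stated analysis uses prognostic information, although some is available before allocation and a regression model that could take it is already planned. Adjusting for variables that predict the outcome narrows the interval and removes part of the chance imbalance between groups, without recruiting anyone else.

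There is also a gap in specification. Fisher's test cannot carry an interaction term, so the primary analysis model mentioned for subgroups is presumably the modified Poisson model. A reader cannot tell what enters that model. If the list is not fixed in advance, it could be chosen after the results are seen.

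What is at stake is some precision and a clear pre-specification. The validity of the primary comparison is not in question.

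**Working it through.** **1. The plan's sample size.** Inputs from section 2-2 (2): rates "between 11% and 4% referring to the previous studies and preliminary program", 5% two-sided, 80% power, about 30% attrition.

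With mean rate 0.075 and difference 0.07, the pooled formula is

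n = [1.960 × √(2 × 0.075 × 0.925) + 0.842 × √(0.11 × 0.89 + 0.04 × 0.96)]² / 0.07² = 221.1, rounded up to 222.

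The continuity correction gives

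(221.1 / 4) × [1 + √(1 + 4 / (221.1 × 0.07))]² = 248.8, rounded up to 249.

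This matches the plan. For attrition, 249 / 0.7 = 355.7, so 356 against the plan's 360; 360 × 0.7 = 252 analysed per group.

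**2. Power of the planned test.** Exact enumeration of Fisher's test at 11% against 4% gives 82.3% at 249 per group and 82.8% at 252. The target is met without adjustment.

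**3. What adjustment adds.** The documents do not say how strongly any baseline variable predicts EPDS at three months, so the correlation is an assumption and is shown as a range. The simulation used 3,000 trials per setting, 249 per group, complete data, one normal covariate, and a latent-normal outcome cut to give 11% and 4%. Modified Poisson models with robust variance were fitted with and without the covariate. The variance gain is 1 / (SE ratio)² − 1; for example, 1 / 0.967² − 1 = 6.9%.

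| Assumed correlation | SE ratio, adjusted / unadjusted | Variance gain | Power: Fisher | Power: unadjusted Poisson | Power: adjusted Poisson | Points from adjustment |
|---|---|---|---|---|---|---|
| 0.2 | 0.995 | 1.0% | 81.6% | 83.6% | 84.1% | 0.5 |
| 0.3 | 0.989 | 2.2% | 83.6% | 86.2% | 87.5% | 1.3 |
| 0.4 | 0.980 | 4.1% | 83.7% | 85.7% | 87.5% | 1.8 |
| 0.5 | 0.967 | 6.9% | 81.2% | 83.8% | 86.7% | 2.9 |
| 0.6 | 0.949 | 11.0% | 82.2% | 84.8% | 89.4% | 4.6 |

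Monte Carlo error is about 0.7 points per power figure. At a correlation of 0.5 the gain is worth 249 × 1.069 = 266 per group instead of 249. A separate simulation (252 per group, 1,500 trials per setting) gave variance gains of 2.1%, 7.1% and 10.9% at 0.3, 0.5 and 0.6, with 0.6, 3.3 and 3.6 power points from adjustment alone (Monte Carlo error about 0.9 points per power figure).

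**4. Separating two effects.** Moving from Fisher to the unadjusted Poisson Wald test already adds 2.0 to 2.6 points in the table. That part is not due to covariates.

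**5. Error rate.** With 7.5% in both groups and correlation 0.5, rejection rates were 3.6% (Fisher), 4.7% (unadjusted Poisson) and 4.5% (adjusted Poisson).

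**6. Which rows apply.** Correlations of 0.5 to 0.6 were chosen with baseline EPDS in mind. Baseline EPDS is not recorded before allocation, so these rows describe mainly a sensitivity analysis. No figure specific to age, parity and expected delivery date can be computed from the documents. If they predict weakly, the 0.2 to 0.3 rows are the relevant guide.

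**The case against.** The strongest case for leaving the plan alone is that an unadjusted comparison is valid under randomisation. Chance imbalance is already covered by its error rate, and its power exceeds the target. The gain from the three variables that can safely enter the primary model is not known and may be about 1% of variance. On this view the choice is largely one of preference. All of that stands as to validity and size. It does not answer the silence about covariates, and the change costs almost nothing.

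Four stronger readings are tempting and are not supported:

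- **That the plan declares the Poisson model unadjusted.** It does not say. The firm evidence for an unadjusted primary comparison is Fisher's test.
- **That the trial discards its strongest predictors.** The documents do not rank predictors. Section 2-1 names other risk factors: persistent fear about pregnancy or delivery, and lack of social support.
- **That baseline EPDS and past mental health problems offer free precision.** Both are self-reported once women know their group, and the baseline voucher is described for controls only. Answers and completion could therefore differ by group. A psychiatric history is fixed before allocation, but the reporting of it is not.
- **That adjustment raises power from 82% to 85% up to 87% to 89%.** That contrast, from the simulation with 252 per group, sets adjusted Poisson against Fisher and so credits adjustment with the change of test. There, adjustment alone adds 0.6 to 3.6 points.

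**Conclusion.** The point holds as an efficiency and specification improvement. The primary test uses no covariates, allocation is unstratified, and the interval model has no stated covariate list, although three usable variables are recorded before allocation. The expected benefit is about 1% to 2% of variance if the assumed correlation is 0.2 to 0.3. It would reach 7% to 11% only at 0.5 to 0.6, which is relevant mainly to an EPDS-adjusted sensitivity analysis. In power, adjustment alone is worth about 0.5 to 5 points over that whole range.

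These sizes rest on one normal covariate, complete data and the plan's own event rates. A reader might infer that the primary analysis is invalid or underpowered; the calculations show neither.

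**What to change.** State in the Statistical analysis plan that the primary risk ratio and its interval come from a modified Poisson model with robust variance, adjusted for age, parity and expected delivery date (age and delivery date as continuous terms). Report the unadjusted risk ratio and Fisher's test alongside, and say which result carries the primary conclusion.

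Keep the list short. At the planned rates, 249 per group gives about 249 × 0.11 + 249 × 0.04 = 37 events.

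Put adjustment for baseline EPDS and past mental health problems in a sensitivity analysis, with a stated rule for missing baseline values. Say there that these items were reported after allocation was disclosed.

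The Statistical analysis plan contains decisions dated after enrolment. If outcomes have already been compared by group, label the adjusted analysis as added afterwards.

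The cost is a short addition to the text, slightly more analysis work, and the missing-data rule for the sensitivity analysis.
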